**Methods:**

Sixty-two people (aged 18–40 years) with a confirmed diagnosis of POTS will be invited to enrol on a feasibility RCT with embedded qualitative study. The primary outcome will be feasibility; process-related measures will include the number of people eligible, recruited, randomised and withdrawn, along with indicators of exercise programme adherence and acceptability. Secondary physiological, clinical and health-related outcomes including sub-maximal recumbent bike exercise test, active stand test and HRQoL will be measured at 4 and 7 months post-randomisation by researchers blinded to treatment allocation. The PostUraL tachycardia Syndrome Exercise (PULSE) intervention consists of (1) individual assessment; (2) 12-week, once to twice-weekly, supervised out-patient exercise training; (3) behavioural and motivational support; and (4) guided lifestyle physical activity. The control intervention will be best-practice usual care with a single 30-min, one-to-one practitioner appointment, and general advice on safe and effective physical activity. For the embedded qualitative study, participants (*n* = 10 intervention, *n* = 10 control) will be interviewed at baseline and 4 months post-randomisation to assess acceptability and the feasibility of progressing to a definitive trial.

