Primary outcome(s)	Feasibility and process indicators: number of patients screened, eligible, recruited, randomised, withdrawn and retained; adherence to exercise rehabilitation programme; length of time to complete each outcome assessment and the whole outcome assessment appointment; willingness of participants to join non-POTS specific exercise rehabilitation programmes; physiological, clinical, patient-reported outcomes to identify a primary outcome for a definitive trial; acceptability of the interventions and the trial (qualitative interviews)
Key secondary outcomes	At 4 and 7 months: exercise capacity—graded recumbent cycle ergometer test; autonomic function—increase in heart rate from supine to 10-min stand; symptom burden—COMPASS 31 dysautonomia scale and fatigue severity scale; HRQoL—EQ-5D-5L; self-efficacy—general self-efficacy scale; exercise tolerability—continuous heart rate monitoring and symptoms during exercise; adverse events. At baseline and 7 months: semi-structured interviews with participants

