#### Component 1: individual assessment and exercise familiarisation

##### Individual assessment:

Participants will undergo a 1-h, one-to-one appointment with a PULSE ‘practitioner’ (clinical exercise physiologist), to assess and record medical and physical activity history and medication and to discuss goals, expectations and any concerns.

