##### Familiarisation sessions:

Exercise instruction will be provided on an individual basis during two one-on-one familiarisation sessions in the first week of the programme, and reinforced throughout, by PULSE practitioners and clinical staff. Familiarisation sessions, conducted within the cardiopulmonary rehabilitation programmes, will enable participants to build confidence, whilst PULSE practitioners refine and optimise the exercise prescription. Behavioural and motivational support will also be introduced during these sessions.

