#### Component 2: supervised out-patient exercise programmes

For the first 6 (of 12) weeks, exercise will be undertaken during one to two sessions per week solely in a controlled gym environment with carefully staged progression in response to participant tolerance and symptoms. For those that are able, moderate intensity dynamic cardiovascular exercise will be prescribed. In addition, ‘functional fitness training’ will aim to improve orthostatic tolerance and general musculoskeletal deconditioning. This type of training is targeted specifically at the components of physical fitness required for activities of daily living, making use of multi-plane motion, to improve agility, coordination, proprioception, balance and functional strength.

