#### Control intervention: best practice usual care

Participants in the control arm will be provided with freely available advice on lifestyle physical activity (POTS UK website) [24] during a one-to-one session, lasting approximately 30 min, with a PULSE practitioner. They will not receive any further input during the control intervention period. Participants will be permitted to continue with any current physical activity but will not receive supervised exercise training or behavioural and motivational sessions from PULSE practitioners.

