### Adverse event management

An adverse event (AE) will be defined as any untoward medical occurrence involving a participant, which does not necessarily have a causal relationship with the intervention or trial. Expected AEs for the PULSE study that will be recorded but not reported include pre-syncope, muscle and joint stiffness, soreness and dislocation and tiredness and fatigue. Any unexpected AEs related to PULSE will be recorded and reported to the TMG. Serious adverse events (SAEs) that have no causal relationship with PULSE will not be reported to oversight committees. Causality and expectedness will be confirmed by the CI with clinician support. SAEs deemed to be unexpected and possibly, probably or definitely related to PULSE will be notified to the Research Ethics Committee (REC) within 15 days. All AEs and SAEs will be recorded within 24 h of the investigator being made aware.

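### Adverse events have many more chances of being recorded in the exercise arm than in the control arm before 4 months, so a pooled between-arm comparison of non-serious events is likely to overstate them under exercise

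*Protocol article*

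**What the plan says.** Four parts of the protocol article bear on this.

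- **Outcome.** Table 1 places adverse events among the key secondary outcomes at 4 and 7 months: "exercise tolerability—continuous heart rate monitoring and symptoms during exercise; adverse events". Data analysis asks for differences in outcomes between arms at those times, with 95% confidence intervals and no hypothesis tests.
- **Recording.** Adverse event management says "All AEs and SAEs will be recorded within 24 h of the investigator being made aware". Pre-syncope, soreness, dislocation and fatigue are expected events; they are to be recorded, although not reported. The end of Secondary outcomes adds that symptoms are noted both at exercise sessions and at assessments.
- **Exercise-arm contact.** The Abstract describes "12-week, once to twice-weekly, supervised out-patient exercise training", and Component 2 gives the same weekly frequency: "For the first 6 (of 12) weeks, exercise will be undertaken during one to two sessions per week". Before that comes a one-hour individual assessment, and exercise instruction is given "during two one-on-one familiarisation sessions in the first week of the programme". Behavioural support every second week is attached to exercise visits, so it adds no visits.
- **Control-arm contact.** There is one session of about 30 minutes, after which: "They will not receive any further input during the control intervention period".

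Both arms attend assessment visits at baseline, 4 months and 7 months.

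**The concern.** If an event enters the record when staff learn of it, the number recorded depends on the number of occasions for learning of it as well as on the number that happen. Here those occasions differ by arm by design, and most for the events that depend most on contact. The Background calls prolonged pre-syncope and fatigue hallmark features of the condition, so they will occur in both arms whatever the treatment, and the article's definition of an adverse event requires no causal link. In the exercise arm such an event can be mentioned to a practitioner within days. In the control arm the next scheduled trial contact may be the 4-month visit.

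Randomisation does not remove a difference in ascertainment, and a confidence interval does not reflect it. A table that makes supervised exercise look less safe than it is could weigh on the decision about a definitive trial, which is what this study is meant to inform.

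**Working it through.** The article gives no adverse event rate, so there is no figure of its own to reproduce on this point. The arm size used below does reproduce: 2 × (1.96 × 17 / 10)² = 22.2, rounded up to 23 per arm, 46 in total; 46 / 0.75 = 61.3, rounded up to 62, or 31 per arm.

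**Step 1. Scheduled intervention contacts before 4 months.** Contacts = weeks × sessions per week + 1 assessment (+ 2 if the familiarisation sessions are additional, which the article does not say).

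| Reading | 1 session/week | 2 sessions/week |
|---|---|---|
| 12 weeks, familiarisation included | 12 + 1 = 13 | 24 + 1 = 25 |
| 12 weeks, familiarisation extra | 12 + 2 + 1 = 15 | 24 + 2 + 1 = 27 |
| 8 weeks, familiarisation included | 8 + 1 = 9 | 16 + 1 = 17 |
| 8 weeks, familiarisation extra | 8 + 2 + 1 = 11 | 16 + 2 + 1 = 19 |

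The 8-week rows arise because the eligibility table (Table 2) speaks of 8–12 weeks, while the Abstract and Component 2 speak of 12. Those passages need to be reconciled. The control arm has 1 contact on every reading.

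**Step 2. Direction.** Let *r* be the share of events recalled at the shared 4-month visit and *q* the chance that an event is picked up at any one session after it occurs. If events are spread evenly over the programme, about half of the *k* contacts follow an event. Take the single control session to fall at the start.

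- Control capture = *r*
- Exercise capture = 1 − (1 − *q*)^(*k*/2) × (1 − *r*)

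Exercise capture exceeds control capture whenever *q* > 0 and *r* < 1. With assumed values *r* = 0.80 and *q* = 0.10:

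- *k* = 13: 1 − 0.9^6.5 × 0.20 = 0.90, against 0.80
- *k* = 25: 1 − 0.9^12.5 × 0.20 = 0.95, against 0.80

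So a good question at 4 months narrows the gap but does not close it if session-captured events are pooled in.

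**Step 3. Size, as illustration only.** With equal true risk in both arms, the apparent risk ratio is simply the ratio of capture shares. All shares here are assumed.

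- 90% against 70%: 0.9 / 0.7 = 1.29
- 90% against 50%: 0.9 / 0.5 = 1.80
- 90% against 30%: 0.9 / 0.3 = 3.00
- equal capture: 1.00

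For an assumed true risk of 40% and capture of 90% against 50%, observed risks are 0.40 × 0.90 = 36% and 0.40 × 0.50 = 20%. With 31 per arm that is about 11 against 6 participants, a spurious difference of 16 percentage points. The 95% half-width is 1.96 × √[(0.36 × 0.64 + 0.20 × 0.80) / 31] = 0.22, or 22 points.

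**The case against.** The strongest reply is that the quoted sentence sets a deadline for entering an event once it is known and does not say how events are sought. The form, wording and recall window of any question are commonly left to the full protocol or the case report form. Table 1 already ties adverse events to 4 and 7 months, visits that both arms attend. This stands in part: the article does not say that collection is purely passive, and a structured question at those visits may exist. It does not settle the matter, because nothing restricts the comparison to events obtained in the same way in both arms, and pooling brings the imbalance back (step 2).

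A reader might infer that harm in controls cannot be detected at all. The documents do not support that. Two shared visits remain, participants attend specialist clinics, and consent covers review of medical notes and telephone contact. The article does not say that these last routes are used for adverse events, but they are not excluded. The statement about no further input describes the control intervention and does not rule out safety contact.

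It is also fair that Data analysis never names adverse events in its sentence on differences, that no test is planned, and that no adverse event contrast is given as a criterion for moving to a definitive trial. The comparison follows from adverse events being a listed outcome and outcome differences being planned. Fatigue and autonomic symptoms are also measured identically in both arms by questionnaire, which gives some protection for those complaints.

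Finally, removing session events from view could hide harms that happen during exercise, such as a dislocation in the gym, and so favour exercise. That objection is sound, and the fix has to respect it.

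**Conclusion.** The point holds for a between-arm comparison that pools all recorded non-serious adverse events. Such a comparison is likely to overstate events in the exercise arm, given 13–25 scheduled intervention contacts (9–27 on every reading) against 1. The direction rests on two modest assumptions: sessions reveal some events, and recall at 4 months is incomplete.

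The size cannot be derived from the article. A reader might take the ratios of 1.3 to 3.0 as an estimate of the bias; they only restate assumed capture shares. Serious events depend less on contact and are less affected. Because no test is planned and intervals will be wide at 31 per arm, the risk is a misleading estimate, not a false positive test. The feasibility outcomes are not touched. This is a worthwhile, inexpensive improvement to how harms are compared.

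**What to change.** 1. At the 4- and 7-month visits, give both arms the same short self-completed adverse event checklist with the same recall window, returned by a route that does not unblind the assessor. Base the between-arm adverse event estimate on it.
2. Report events captured at exercise sessions in full beside that estimate, labelled by source and with sessions as the denominator, so that harms during exercise stay visible.
3. Keep the recording of serious adverse events continuous in both arms.

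The cost is a short form at two existing visits and a reporting rule. The drawback is that session events not recalled on the checklist fall outside the between-arm estimate; this must be stated next to it. Participants also know their allocation, so the checklist equalises the opportunity to report, not every influence on reporting.

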### Patient and public involvement

The PULSE intervention components were initially developed based on existing evidence, previous clinical work at our centres and extensive patient and public involvement (PPI). Eighteen people with POTS participated in teleconference consultation prior to the grant funding application. The intervention was further developed and refined during two co-creation workshops with multiple stakeholders (as outlined in more detail above). Lay representatives will sit on the TMG and will be invited to contribute to dissemination and reporting on completion of the study.

## Discussion

Postural orthostatic tachycardia syndrome can be a debilitating condition, with pre-syncope and fatigue, amongst other symptoms, significantly impacting on activities of daily living and HRQoL. Whilst prevalence is estimated to be between 0.2 and 1%, it is increasingly recognised that POTS is commonly misdiagnosed, thus prevalence is likely to be much higher. In the absence of effective and appropriately tested medical and pharmacological therapies, lifestyle interventions have the potential to improve symptoms and help manage this long-term condition.

Exercise rehabilitation is not routinely offered to people with POTS as it has not been evaluated in well-designed clinical trials. Preliminary reports from non-randomised controlled studies indicate that exercise rehabilitation programmes, as provided almost universally for people with long-term cardiac and pulmonary conditions, may be beneficial for people with POTS. The PULSE study will be the first to assess the feasibility of an exercise intervention with behavioural and motivational support for people with POTS, to inform whether or not a future multi-centre RCT investigating clinical and cost-effectiveness can be delivered in the NHS. The feasibility of a supervised exercise programme, a behavioural and motivational support intervention, and a number of important clinical, physiological and patient-reported outcome measures, will be evaluated within the framework of a feasibility RCT. If feasibility is proven, a definitive multi-centre RCT should be conducted in the future.

## Trial status

All approvals are in place, and the trial is ready to begin recruitment. Currently, all trial activities have been temporarily suspended due to the COVID-19 pandemic.

## Data Availability

The datasets used and/or analysed during the current study will be available from the corresponding author on reasonable request.

## Abbreviations

ADePT: A Process for Decision-making after Pilot and Feasibility Trials
AE: Adverse event
CMO: Chief Medical Officer
CI: Chief investigator
COMPASS-31: Composite autonomic symptom score
CONSORT: Consolidated Standards of Reporting Trials
FSS: Fatigue Severity Scale
GCP: Good Clinical Practice
GDPR: General Data Protection Regulation
HADS: Hospital Anxiety and Depression Scale
HRQoL: Health-related quality of life
HSD: Hypermobility spectrum disorders
IRAS: Integrated Research Application System
ISRCTN: International Standard Randomised Controlled Trial Number
PI: Principle investigator
POTS: Postural orthostatic tachycardia syndrome
PPI: Patient and public involvement
RCT: Randomised controlled trial
REC: Research Ethics Committee
R&D: Research and development
RPE: Rating of perceived exertion
SAE: Serious adverse event
SAP: Statistical analysis plan
SD: Standard deviation
SOP: Standard operating procedure
UHCW: University Hospitals Coventry & Warwickshire
WHO: World Health Organization
